### Randomization

Patients will be randomized 1:1 to either upfront ALND (control) or TAD (intervention). Randomization lists will be prepared using randomly permuted blocks of sizes 6 and 8 and will be stratified by site. Further stratification factors, such as type of breast surgery, received RT, and subtype, were considered but will instead be handled in sensitivity analyses. The randomization lists will be produced using the statistical software package Stata^®^ (StataCorp. 2023. Stata Statistical Software: Release 18. College Station, TX, USA: StataCorp LLC), and will then be uploaded into the REDCap electronic case report form system. Personnel enrolling participants and those who assigning them to their respective groups will not have access to the random allocation sequence. This is not a blinded trial, and it will not be possible to mask treatment assignment from trial personnel. The trial statistician will be blinded to participants’ randomized allocation until the target number of events has been observed and the final data set is downloaded.

### Adjuvant treatment

Systemic adjuvant treatment is to be administered in accordance with national or institutional guidelines.

RT follows national or institutional guidelines, as detailed in *Table 3*. Target volumes must be delineated as separate clinical target volumes according to European Society of Radiotherapy and Oncology guidelines^19^. Dose, fractionation, and treatment time must be used in accordance with relevant national or institutional guidelines. The recommended dose in locoregional RT is 40 Gy in 15 fractions given 5 days/week. Details on RT must be reported prospectively in the trial database. A comprehensive quality assurance of RT will be performed to underpin the conclusions of the trial endpoints. For this purpose, sites are encouraged to continuously submit each participant’s treatment plan for central review. As a minimum, the first five RT plans should be submitted; thereafter, every second to third plan should be submitted in the order of enrolment.

**Table 3 zrag083-T3:** Radiotherapy summary

Whole breast radiotherapy	Mandatory after breast-conserving surgery (that is, partial breast radiotherapy is not accepted)
Chest wall irradiation after mastectomy	According to institutional guidelines
Regional lymph node radiotherapy	According to institutional guidelines
Tumour bed boost	According to institutional guidelines
Volume definition	The remaining breast/chest wall and each lymph node level must be delineated as separate volumes according to ESTRO guidelines
Organs at risk	The heart, ipsilateral humeral head, ipsilateral lung, and spinal canal must be delineated for all patients
Reporting/quality assurance	Radiotherapy details reported to the trial database for all patients; radiotherapy plans submitted for central review

ESTRO, European Society of Radiotherapy and Oncology.

### Monitoring and follow-up

Each patient is to be followed up for 10 years after surgery in accordance with national and/or regional follow-up schedules. The minimum follow-up includes annual imaging (mammography, ultrasound and/or magnetic resonance imaging), with or without clinical examination, for 5 years and then imaging every 2 years, with or without clinical examination or telephone contact. Telephone contact at 5 years is mandatory. However, data on ongoing treatment, recurrence, and survival must be completed annually until 10 years after enrolment, even if the patient has not been to a clinical examination or imaging follow-up.

### Estimated sample size and power

The aim of this trial is to show that the intervention is non-inferior to the standard of care regarding the primary endpoint of RFS. In the SENOMAC trial, patients in whom ALND was omitted had an estimated 5-year RFS of 89.7%^4^, which is comparable to recently reported rates in similar trials such as in the two randomization groups of the INSEMA trial’s second randomization^20^ (invasive disease-free survival 86.6% and 93.8%, respectively) and of the SINODAR-ONE trial (RFS 96.4% and 95.6%, respectively)^7^. The higher clinical risk in SENOMAC-ULTRA, including patients with higher nodal stages than SENOMAC, should be balanced by the fact that CDK4/6 inhibitors have become the standard of care for patients with oestrogen receptor-positive breast cancer^21^, who are expected to be the predominant population in SENOMAC-ULTRA, just as in SENOMAC (93.4%)^4^.

Thus, assuming a 5-year RFS rate of 89.7% in both groups, the study aims to show that the 5-year RFS is non-inferior in the intervention arm using a non-inferiority margin of 4.5% (that is, 5-year RFS of 85.2%). The non-inferiority margin was selected to be lower than the non-inferiority margin in similar trials (for example, 5% in the TAXIS trial^13^ and 6% in the Alliance A011202 trial^22^). Based on this, the study needs to show that the upper limit of the 90% confidence interval (equivalent to a one-sided alpha of 0.05) of the hazard ratio is below 1.47. Using the method described by Jung *et al*.^23^ gives a sample size of 1230, recruited equally over 5 years and a total trial duration of 9 years, with 162 events required for 80% power. However, because recruitment is expected to be slower in the first 2 years, a simulation was used to investigate the effect of this on the required sample size. Assuming exponential survival times and non-proportional recruitment over time, the total sample size increased to 1380 and achieved power increased to 81%. Simulation was performed in Stata^®^ (StataCorp. 2023. Stata Statistical Software: Release 18. College Station, TX, USA: StataCorp LLC), using 10 000 simulated data sets.

### Statistical analysis

The primary endpoint of RFS will be used to estimate the hazard ratio between the two trial groups using a Cox proportional hazards regression model. Non-inferiority will be declared if the upper bound of the 90% confidence interval of the estimate of the treatment effect is lower than 1.47. The model will adjust for strata used in the randomization procedure (site); no other preplanned covariate adjustment will be performed. If there is strong evidence of non-proportional hazards for the treatment parameter, a restricted mean survival time at 5 years after randomization will be used to estimate the effect of the treatment and an absolute inferiority margin of 4.5% will be used.

Analysis will be performed in both the intention-to-treat and per-protocol populations, with equal weight given to each result, following current European Medicines Agency guidelines^24^. If European Medicines Agency guidance changes while the trial is underway, consideration will be given to adapting the statistical approach to follow best practice and the guidelines in place at the time the final analysis is performed.

Secondary endpoints will be assessed according to the same principles as the primary endpoint. All non-inferiority endpoints will be assessed using the lower or upper (as appropriate) bound of a 90% confidence interval. All superiority endpoints will be assessed using a two-sided alpha of 0.05. More details will be provided in the statistical analysis plan, which will be written, approved, and made publicly available before the trial statistician accesses unblinded data.

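### The non-proportional-hazards fallback sets a survival-probability margin of 4.5% against a restricted mean survival time, where it is undefined and could mislead in either direction

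*Protocol article*

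**What the plan says.** In the protocol article, Estimated sample size and power, the margin is a difference in the probability of being event-free at 5 years. The design starts from "assuming a 5-year RFS rate of 89.7% in both groups" and proceeds "using a non-inferiority margin of 4.5% (that is, 5-year RFS of 85.2"%. This is converted to a hazard ratio of 1.47, to be excluded by the "upper limit of the 90% confidence interval (equivalent to a one-sided alpha of 0.05").

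Statistical analysis carries this into the primary rule: "Non-inferiority will be declared if the upper bound of the 90% confidence interval of the estimate of the treatment effect is lower than 1.47".

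The same section then gives a conditional alternative. Given strong evidence of non-proportional hazards for treatment, the effect measure becomes RMST ("a restricted mean survival time at 5 years after randomization will be used"), which "will be used to estimate the effect of the treatment and an absolute inferiority margin of 4.5% will be used". No time unit, conversion or base for the percentage is given. Further detail is deferred to a statistical analysis plan that is to be made public before unblinding.

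**The concern.** RMST to 5 years is the area under the RFS curve up to 5 years, so a treatment difference in RMST is in years or days. A 4.5-point difference in the height of the curve at 5 years is a different quantity. The protocol recognises this for the hazard ratio, where it converts the margin to 1.47. It makes no such conversion for RMST.

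The sentence is a decision rule for the primary endpoint. Once triggered, it decides whether targeted axillary dissection (TAD) is declared non-inferior to axillary lymph node dissection (ALND). An analyst would have to choose what 4.5% means, and the candidate readings differ up to fivefold. The lenient ones tolerate a loss of 8 points or more under the design's survival model, although the protocol says that it chose 4.5% to be tighter than the 5% and 6% of similar trials. The strict one would probably fail a TAD arm that is truly equivalent.

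**Working it through.** **Inputs.** From Estimated sample size and power: 5-year RFS 89.7% in both arms, 85.2% at the margin, exponential survival, one-sided alpha 0.05, 1380 patients in total. From Randomization: 1:1 allocation, so 690 per arm.

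**The plan's own figures.**
- Hazard ratio at the margin: ln(0.852)/ln(0.897) = 1.4735, stated as 1.47.
- Events by the Schoenfeld formula: 4 × (1.645 + 0.842)² / (ln 1.4735)² = 165, within 3% of the stated 162 ("with 162 events required for 80% power").
- For 1230 patients with uniform accrual over 5 of 9 years, the event probability is 1 − (e^(−4λ) − e^(−9λ))/(5λ) = 0.1314 with λ = 0.02174. Then 1230 × 0.1314 = 161.6 events.

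The design figures therefore reproduce, which confirms that 4.5% is a probability difference.

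**The same margin as RMST.** Under exponential survival, RMST(5) = (1 − e^(−5λ))/λ.
- Control: λ = −ln(0.897)/5 = 0.02174, RMST = 0.103/0.02174 = 4.738 years.
- At the margin: λ = −ln(0.852)/5 = 0.03203, RMST = 0.148/0.03203 = 4.620 years.
- Loss: 0.118 years, or 43 days. That is 2.35% of 5 years and 2.48% of the control RMST.

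**Possible readings of 4.5%.** For each, the TAD hazard that produces that RMST loss was solved for. With 690 per arm and no censoring before 5 years, the standard error of the RMST difference is 0.0485 years with equal arms and 0.0532 years at the margin. Power is Φ(m/0.0485 − 1.645). False non-inferiority at a true 85.2% is Φ((m − 0.1177)/0.0532 − 1.645).

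| Reading | Margin m (years) | 5-year RFS tolerated | Hazard ratio | Power, equal arms | False non-inferiority at 85.2% |
|---|---|---|---|---|---|
| 0.045 years | 0.045 | 88.0% | 1.18 | 24% | 0.1% |
| Matched to 85.2% | 0.118 | 85.2% | 1.47 | 78% | 5% |
| 4.5% of control RMST | 0.213 | 81.6% | 1.87 | 99.7% | 56% |
| 4.5% of 5 years | 0.225 | 81.2% | 1.92 | 99.9% | 65% |

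A simulation of 4000 trials per scenario, with follow-up assumed uniform from 4 to 9 years, agreed: power 24%, 79%, 99.6% and 99.7%; false non-inferiority 0.2%, 5.0%, 57% and 65%.

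**When hazards are not proportional.** This is when the fallback applies. The control was kept exponential and the TAD arm fixed at 85.2% at 5 years, with a Weibull curve S(t) = 0.852^((t/5)^k).
- k = 0.5 (early separation): RMST loss 0.241 years.
- k = 1: 0.118 years.
- k = 1.5: 0.043 years.
- k = 2 (late separation): −0.008 years.

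One and the same 5-year loss of 4.5 points thus gives RMST losses from about 0.24 to −0.01 years, and no single conversion exists. In simulation with accrual assumed at 10/15/25/25/25% per year, a 0.118-year margin declared non-inferiority in 0% of trials at k = 0.5 and about 88% at k = 2. The 0.225-year margin did so in about 3% at k = 0.5. The Kaplan-Meier difference at 5 years against 4.5 points stayed near 5% for early, constant and late separation, with about 85% power when the arms are equal.

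**The case against.** Four points can be made for the plan.

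**The fallback is conditional and more detail is promised.** Both are true. The primary Cox rule, the event target and the sample size do not depend on this sentence. But the article does not leave the matter open: it names the estimator, the horizon and the margin. An analysis plan that repeats the sentence inherits the mismatch, and one that departs from it alters a published primary decision rule.

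**4.5% of 5 years has a coherent meaning.** A constant 4.5-point gap over the whole 5 years has area 0.045 × 5 = 0.225 years, so this can be read as an average absolute survival difference. That stands as a possible intention. It is still not the margin that the design defines, which is the gap at 5 years, and the article does not say that it is meant.

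**The error rates are computed where the fallback does not apply.** This stands. The 65% and the hazard-ratio equivalents come from proportional exponential hazards, under which the Cox test decides. With early separation the 0.225-year reading is not lenient at all (about 3%).

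**No reading is fixed.** A reader might infer that the fallback would give a wrong verdict, or that it would pass a clearly inferior TAD arm. The documents do not support this. They do not choose between 0.225, 0.213 and 0.045 years, nothing marks one as the usual or intended reading, and the word absolute speaks against the percentage of control RMST. A result far from the margin would get the same verdict under any reading.

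**Conclusion.** The sentence is wrong as written. It pairs a time-scale estimator with a probability-scale margin, so the margin is undefined for the fallback, and the verdict could err towards false non-inferiority or towards failing an equivalent TAD arm.

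The size can only be illustrated. Under the protocol's exponential assumption with 690 per arm, the plausible readings run from a hazard ratio of 1.18 with about 24% power to 1.92 (an 8.5-point loss) with about 65% false non-inferiority at a true 85.2%. Each figure holds for one reading under proportional hazards, and none is the fallback's error rate in use. The matched value of 0.118 years is equally tied to that assumption.

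This should be fixed, but it does not undermine the design: the primary Cox rule with 1.47 stands.

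**What to change.** Before unblinding, replace the fallback sentence with one that keeps the margin on its own scale. Suggested wording: *If there is strong evidence of non-proportional hazards, the treatment effect will be the difference in Kaplan-Meier 5-year RFS (ALND minus TAD), and non-inferiority will be declared if the upper bound of its 90% confidence interval is below 4.5 percentage points.*

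If RMST is preferred, state its margin in years or days with its own justification, and say that 0.118 years matches 4.5 points only under proportional exponential hazards. RMST could also be reported as a supportive estimate without a margin.

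The cost is one sentence, repeated in the statistical analysis plan. It needs no further patients, data or follow-up.

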### Ethics and dissemination

The trial protocol has been approved by the Swedish Ethical Review Authority (Dnr 2025-07730-01). Each participating country will obtain their own ethics permissions based on the currently valid trial documents.

ALND is routinely performed without preoperative axillary marking procedures. For participants randomized to the intervention group, the marking procedure may result in discomfort and potentially temporary pain, a haematoma, or, rarely, an infection. In addition, a degree of increased risk for axillary recurrence among individual patients who do not undergo ALND cannot be ruled out. However, studies in which patients received systemic treatment according to modern standards for lymph node-positive patients showed no impact of reduced extent of axillary surgery on survival or risk of recurrence, including axillary recurrences^1,3,4,7^. In addition, this potential risk increase must be weighed against the significant benefit of less arm morbidity associated with less extensive surgery. ALND is currently increasingly abandoned in diverse patient populations, and there is a risk that ALND omission will be implemented in routine care or individual practice before sufficient evidence is available, which is why it is crucial to explore this approach in a trial.

Publications of the primary and secondary endpoints are collaborative efforts by steering committee members, statisticians, advisors, the RT quality assurance team, central trial coordinator, and patient representatives, who are all included as members of The SENOMAC-ULTRA Trialists Group.

## Data Availability

Deidentified participant data may be made available upon reasonable request to the coordinating investigator if accompanied by all relevant ethical and legal permissions. The earliest date of data sharing is 3 months after the publication of the primary endpoint. Any request for data will be discussed in the international steering committee, and only requests that fulfil all necessary requirements will be accepted.
